**Statistical Analysis**

Statistical analysis will be done using SPSS software, version 18.0 (Chicago, IL, USA) and it will be conducted according to intention-to-treat analysis for patients in the group to which they were allocated. Baseline demographic and clinical variables will be compared between groups with independent Student t-tests and 2 test of independence. The primary evaluation will be repeated measured analyses of covariance (ANCOVA) with time as the within-subject factor and group as the between-subject factor and adjusted for baseline outcomes for evaluating between-group differences in outcomes. We will use χ2 tests to compare self-perceived improvement at 6 and 12 months in both groups. To enable comparison of effect sizes, standardized mean score differences (SMDs) will be also calculated by dividing the mean score differences between groups by the pooled standard deviation.

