**Outcome Measures**

Clinical records of all patients will include questions regarding the location of the symptoms, aggravating/relieving factors, intensity, duration of the pain and previous treatments. They also complete the BDI-II for assessing symptoms of depression. The outcomes include pain, function, symptoms severity, and self-perceived improvement.

The intensity of pain will be assessed with an 11-point Numerical Pain Rating Scale (NPRS, 0: no pain; 10: maximum pain) (23). We will assess the patients’ current level of pain and the worst level of pain experienced in the preceding week. Farrar et al determined that a change of 2 points or a 30% decrease in pain intensity from baseline can be considered as a minimal clinically important difference (MCID) for the intensity of pain in patients with chronic conditions (24). For patients with bilateral symptoms, we designated the study hand on the basis of the more self-reported symptomatic hand; if symptoms were equivalent, the mean pain of both hands was considered.

The Spanish version (25) of the Boston Carpal Tunnel Questionnaire (26) (BCTQ) will be used to assess function and severity of the disease. This questionnaire evaluates 2 domains: a) the functional status scale assessing ability to perform 8 common hand-related tasks; b) the symptom severity scale including 11 items assessing pain severity, numbness, and weakness at night and during the day. Each question is answered on a 5points scale (1: no complaint; 5: severe complaint). Higher scores indicate greater severity or worse function. This questionnaire has been shown to be valid, reliable, and responsive for individuals with CTS (27). A change of 0.74 points in the function subscale and 1.14 points in the symptom subscale can be considered as MCID of the BCTQ (28).

Finally, self-rated improvement will be assessed with a Global Rating of Change (GROC), which consists of a 15-point scale ranging from -7 (a very great deal worse) to +7 (a very great deal better) (29).Descriptors of worsening or improving are assigned with values ranging from -1 to -7 and +1 to +7, respectively (30).It has been reported that scores of +4 and +5 are indicative of moderate changes in patient status, whereas scores of +6 and +7 indicate large changes in the status of the patient.

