Pain and function will be assessed at baseline, and 1, 3, 6, and 12 months after the end of therapy, whereas GROC will be assessed at 6 and 12 months by an assessor blinded to the subject’s allocation.

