**Sample size determinations**

We determined two sample size determination based on pain and function outcomes. For pain intensity, sample size calculation was calculated to detect treatment differences of 2.0 units on pain (MCID), assuming a standard deviation of 3.0,a 2-tailed test, an alpha level (α) of 0.05 and a desired power (β) of 90%. The estimated desired sample size with pain intensity as the main outcome was calculated to be at least 50 subjects per group. A dropout rate of 15% was expected, so around 60 patients should be included in each group.

For function, sample size calculation was determined to detect between-groups treatment differences of 0.5 points (MCID) on function subscale, assuming a standard deviation of 0.7,a 2-tailed test, an alpha level (α) of 0.05 and a desired power (β) of 90%. The estimated desired sample size with function as the main outcome measure was calculated to be at least 45 subjects per group. A dropout rate of 15%-20% was expected, so around 60 patients should be included in each group.

We decided to include pain as the main outcome in this study for the following reasons: 1, pain within the median nerve-related areas is the most common symptom experienced by patients with CTS (31); 2, pain is mainly determined by the activity of peripheral nerve nociceptors and continuous nociceptive afferent bombardment from the nerve nociceptors can lead to central and peripheral sensitization mechanisms observed in these patients (32).

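### The chi-square tests planned for the global rating of change ignore the order of its 15-point scale and give up power; an ordinal comparison is a cheap improvement

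*Protocol*

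**What the plan says.** Outcome Measures (protocol) lists self-perceived improvement as one of four outcomes. It is measured by GROC, with 15 ordered points from -7 (worst) to +7 (best). The section describes two bands: "scores of +4 and +5 are indicative of moderate changes in patient status, whereas scores of +6 and +7 indicate large changes". It does not adopt either as a definition of success. The timing is that "GROC will be assessed at 6 and 12 months".

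Statistical Analysis gives the comparison in one sentence, as chi-square "tests to compare self-perceived improvement at 6 and 12 months in both groups". It does not say whether the table has all 15 points, the described bands or a two-way split, and it names no trend version of the test.

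Under Sample size determinations the protocol states: "We decided to include pain as the main outcome in this study". GROC plays no part in the sample size.

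**The concern.** The Pearson chi-square statistic is unchanged if the columns of the table are shuffled. It therefore treats a move from +3 to +4 like a move from +3 to -7. When one treatment tends to give higher ratings than the other, the test spreads its sensitivity over many patterns that are not of interest and has less power for the one that is. Reducing the scale to bands or two groups removes the surplus degrees of freedom, but it also removes the differences within each group.

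At stake is how a GROC result can be read. A real difference of moderate size in patients' own rating could easily be reported as not significant because of the choice of test, although the same data, ranked, would have had a clearly better chance of showing it.

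**Working it through.** **Numbers available.** No figure is stated for GROC, so the group size comes from the pain calculation: "treatment differences of 2.0 units on pain (MCID), assuming a standard deviation of 3.0", two-sided alpha 0.05, power 90%.

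- n per group = 2 × (1.960 + 1.282)² × 3.0² / 2.0² = 47.3, so 48 (49 with the t distribution). The protocol's figure, "calculated to be at least 50 subjects per group", is reproduced within rounding.
- Dropout of 15%: 50 / 0.85 = 58.8, so 59, against about 60 stated.

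The GROC comparison will therefore have about 50 to 60 women per arm.

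**Sparsity if all 15 points are used.** The mean expected count per cell is 50/15 = 3.3, or 60/15 = 4.0. In simulation about 9 to 13 categories were occupied. After empty ones were dropped, 37-59% of the remaining cells still had an expected count below 5.

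**Power (assumed distributions).** Ratings were drawn from a normal distribution, rounded to the scale and capped at ±7, with a pure shift between arms. Rejection is at two-sided 5%, without continuity correction. With 2,000 to 3,000 simulated trials per row, the simulation error is about 1 percentage point.

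Shift of half an SD, 50 per arm, means placed symmetrically about the centre shown:

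| Centre, SD, shift | Chi-square, 15 points | Split at +4 | Split at +6 | Mann-Whitney |
|---|---|---|---|---|
| 3.5, 2.5, 1.25 | 24% | 53% | 43% | 68% |
| 3, 3, 1.5 | 22% | 51% | 40% | 67% |
| 4.5, 2, 1 | 30% | 48% | 46% | 66% |

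A three-band table (below +4, +4/+5, +6/+7) gave 47% in a run where the 15-point table, the +4 split, the +6 split and Mann-Whitney gave 23%, 51%, 43% and 67%.

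Shift of 0.6 SD (1.5 points, SD 2.5):

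| Means, n per arm | Chi-square, 15 points | Split at +4 | Split at +6 | Mann-Whitney |
|---|---|---|---|---|
| 3 and 4.5, n = 50 | 39% | 68% | 59% | 82% |
| 4 and 5.5, n = 50 | 39% | 60% | 64% | 80% |
| 3 and 4.5, n = 60 | 47% | 75% | 68% | 89% |

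**Hand check of one entry** (means 3 and 4.5, split at +4, n = 50):

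- Success rates: 1 - Φ((3.5 - 3)/2.5) = 0.42 and 1 - Φ((3.5 - 4.5)/2.5) = 0.66.
- Average rate 0.54; standard error √(2 × 0.54 × 0.46 / 50) = 0.0997.
- z = 0.24 / 0.0997 = 2.41; power ≈ Φ(2.41 - 1.96) = 67%, against 68% simulated.

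**Larger effect.** At a shift of 2.0 points (SD 2.5, n = 50), the splits reach 86-87%, three bands 90% and Mann-Whitney 97%. The ranking is the same but the gap is smaller.

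**No true difference.** The 15-point chi-square rejects in about 4%, a single split in just under 6%, three bands in 4.9% and Mann-Whitney in about 5-6%. Each test used alone roughly holds its level, so the cost is power.

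**The case against.** The strongest reply is that the sentence can be read as a comparison of the proportions of women improved, or of women in each described band. That is an ordinary and valid use of chi-square. It gives clinicians a figure they can read, and a three-band table needs no choice between two cut-offs. The 15-point table is only one possible reading, and arguably the less natural one. All of this stands. What remains is that the banded and split versions also had less power than the rank test in every scenario examined.

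A reader might infer four stronger things, none of which the protocol supports:

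- *That the plan has both sparse cells and an open cut-off.* These belong to alternative readings. Sparse cells arise only if the scale is left whole; a cut-off matters only if it is split.
- *That the cut-off will be chosen after the data are seen.* A responder threshold for an outcome other than the main one may well be fixed in a statistical analysis plan that is not at hand.
- *That the false-positive rate is inflated.* Reporting the best of the 15-point table and the two splits would reject in about 10-13% under no difference, and the best of the two splits alone in about 8-10%. Nothing in the protocol says that such picking will occur.
- *That low power here favours the trial's similarity hypothesis.* The Hypothesis section words that for function and pain, not for GROC. A non-significant GROC result might be cited loosely in support, but it is no test of that hypothesis.

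**Conclusion.** The point holds as an efficiency problem, not as an invalid analysis. The named test does not use the order of the scale on any reading of the sentence. With 50 per arm and a half-SD shift, power is about 22-30% on the raw scale, 40-53% after a split or banding, and 66-68% with Mann-Whitney. At 0.6 SD the figures are 39%, 59-68% and 80-82% (raw, splits, Mann-Whitney), and the difference shrinks further as the effect grows.

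The sizes rest on assumed rounded-normal ratings and a uniform shift. The protocol supplies neither, and the advantage of a rank test could be smaller if the treatments differed in spread rather than in level. GROC is not the main outcome, and the repeated-measures analysis of pain and the sample size are untouched. Severity is low; this is a cheap improvement.

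**What to change.** Replace the chi-square sentence in Statistical Analysis with one that compares GROC between groups at 6 and at 12 months on the full scale, by a Mann-Whitney test or a proportional-odds model. Add, as description, one responder proportion fixed in advance, with its risk difference and 95% confidence interval. A score of +4 or higher is one example that matches the moderate-or-larger change already described in Outcome Measures. If a chi-square test is kept instead, state the bands or the split in advance and accept the lower power.

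The cost is a sentence or two, with the same data. There is a small downside: a rank test gives an effect that is harder to read, and a proportional-odds model adds an assumption to be checked. The responder proportion makes up for the first.

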**Pre planned Secondary Analysis**

The existence of individuals’ differences in the response to painful stimuli suggests that potential genetic factors can be involved in nociceptive modulation. The catechol-O-methyltransferase (COMT) gene is one of the several potential genetic determinants for nociceptive processing; however, its role in chronic pain remains still controversial. The Val158Met single-nucleotide polymorphism of the COMT leads to a substitution of valine (Val) with methionine (Met) at codon 158 on chromosome 22q11. This enzyme is involved in the metabolic degradation of several neurotransmitters such as dopamine, norepinephrin, and epinephrine. Previous studies have tried to identify the association of Val158Met genotype with the presence of chronic musculoskeletal pain; however, the results are conflicting. The only study investigating genetic influence in CTS found that the presence of the Met/Met genotype of the COMT gene was not a risk factor for the development of CTS, but it was associated with worse clinical pain presentation of the patients: higher intensity of pain, higher symptoms severity, and lower function (33). These recent results would suggest a regulating role of Val158Met polymorphism in the phenotypic expression of CTS. We do not know if this genotype can be also associated with treatment response.

The Val158Met polymorphism has been found to modulate treatment efficacy of morphine in cancer patients with pain. The presence of the Met/Met genotype induces less consumption of morphine than the Val/Val genotype (34). No previous study has investigated the potential influence of the Val158Met genotype in treatment outcomes in CTS. Therefore, a secondary analysis will be conducted to investigate the association of the Val158Met polymorphism with pain and function in CTS. We hypothesized that women with CTS carrying Met/Met genotype would exhibit worse long-term treatment outcomes than those carrying the Val/Val or Val/Met genotypes.

# DNA Collection and COMT Genotyping

At the beginning of the trial, non-stimulated whole saliva samples will be collected from each participant into collection tubes (passive drooling technique) according to the standardized procedures. The following instructions will be given to participants for saliva collection: 1, all participants will be abstained from any kind of vigorous exercise through the previous week; 2, those who smoke will be asked not to do so from 2 days before the collection sampling; 3, they will be asked not to eat or drink or chew gum for 1 hour before the sampling. We will use saliva instead of blood sampling because saliva collection is a non-invasive, stress-free and ethic suitable assessment method.

Immediately after collection, samples will be centrifuged at 3000 rpm for 15 min to obtain the cell sediment and they were stored at -20º C until the analysis. Genomic DNA will extracted from saliva sediments using “Genomic DNA extraction and purification Kit” (Real Molecular Biology) following the manufacturer’s instructions. The single Val158Met (rs4680) nucleotide polymorphism will be properly genotyped using a TaqMan® Drug Metabolism Genotyping Assay on a Real Time PCR ABI Prism 7000 Sequence Detection System (APPLIED BIOSYSTEM, USA) in a Genomic Unit (Centro de Apoyo Tecnológico, Universidad Rey Juan Carlos, Madrid, Spain). The 3 possible haplotypes will be associated with different fluorescent dyes to determine the identification of the genotypes: Val/Val, Val/Met, or Met/Met. The results are derived from a G→A substitution at the following sequence:

CCAGCGGATGGTGGATTTCGCTGGC [A/G] TGAAGGACAAGGTGTGCATGCCTGA

